### Confidentiality

Participant data are strictly confidential, and all personally identifiable information (PID) is securely stored on NHS or University drives with access granted only to the research team with password protection. Paper forms for questionnaires are pseudo-anonymised with a Participant Identification Number (PIN) and are secured in locked NHS or University spaces separate to PID. Participants are made aware of the security and confidentiality of the data including the mandated limits to confidentiality when the study team is provided with information that indicates the participant or another person is deemed to be a risk to self or others. Audio recordings are carried out in line with the sites NHS policies and procedures. Audio recordings are transferred to a secure NHS drive and are only accessible by members of the research team with delegated responsibility to access, as per the study delegation log.

## Statistical methods

### Statistical methods for primary and secondary outcomes

A detailed statistical analysis plan will be prepared and approved by the Trial Management Group (TMG), Data Monitoring Committee (DMC) and TSC prior to the interim analysis.

Descriptive statistics within each randomised group will be presented for baseline values. These will include counts and percentages for binary and categorical variables, and means and standard deviations, or medians with lower and upper quartiles, for continuous variables, along with minimum and maximum values and counts of missing values. There will be no tests of statistical significance or confidence intervals for differences between randomised groups on any baseline variable.

For the analysis of the primary outcome at both stages, we will use a generalised linear model that includes fixed effects for treatment, diagnosis and site using maximum likelihood estimation. For each pairwise comparison with TAU, we will report the difference in proportion of admissions as the estimate of treatment effect with 2-sided 95% confidence intervals and 1-sided *p* values.

Secondary outcomes with repeated measures at 3 and 6 months will be analysed at stage 2 only. These will be analysed with generalised linear mixed models (GLMMs) appropriate for the distribution of the outcome using maximum likelihood estimation. Fixed effects will be treatment, diagnosis, site, time and time*group interactions, with a random effect for participant. Treatment effect estimates will be reported as adjusted between-group mean differences in outcomes between the groups separately at 3 and 6 months with 2-sided 95% confidence intervals and 1-sided *p* values.

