### Unplanned trial adaptations

Several important changes to the design occurred after the trial commenced, which were unplanned changes to the design. In line with the Adaptive Designs CONSORT Extension (ACE) statement [30], we report the unplanned changes in this protocol. All changes were approved by the funder, and where regulation was required, was approved by the Medicines and Healthcare Products Regulatory Agency (MHRA), the UK Research Ethics Committee (REC) and Health Research Authority (HRA).

In response to feedback from NHS crisis teams regarding the duration of care, the inclusion criteria was changed from ‘*Receiving care from a HBTT (referrals to HBTT Team are associated with increased risk of a psychiatric hospital admission in the near future)*’ to ‘*Currently receiving care from a Home-Based Treatment Team/Crisis team or have done so within the last 14 days, since referrals to HBTT/Crisis Team are associated with increased risk of a psychiatric hospital admission in the near future*’. In response to feedback from crisis teams regarding the patient population diagnoses, we was advised to include patients with a post-traumatic stress disorder (PTSD) or complex PTSD (cPTSD) diagnosis. As such the inclusion was changed to include patients with these diagnoses to ensure generalisability of the study findings to the crisis team patient population.

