Since the initial development of this protocol, the BrighterSide smartphone app has been evaluated in a large study of 550 participants from the general population who reported suicidal ideation and results showed there was no significant improvement for the primary outcome of suicidal ideation in comparison to the waitlist control group [24]. In response to the new scientific data, the RAPID design was changed from a four-arm trial to a three-arm trial following removal of the BrighterSide intervention arm. The decision was made in conjunction with the RAPID trial Data Monitoring Committee (DMC), Trial Steering Committee (TSC), the study sponsor and the funder. The following changes were made to the design:i.Randomisation ratio changed from 1:1:1:2 favouring TAU to 2:2:3 favouring TAU.ii.Target sample size changed from 1235 to 1064 (not inclusive of the 54 participants randomised to BrighterSide at the time of dropping this arm) with no loss of power.iii.Number required for the interim analysis will change from the first 559 participants recruited with available primary outcome data to first 385 PREVAIL, SAFETEL and TAU participants with primary outcome data and provide 92% power.iv.Removal of the following exclusion criterion since it was relevant only to the BrighterSide app, ‘*visual impairment, severe enough to prevent engagement with the BrighterSide app as provision would be impossible on both financial and logistical ground*’.v.The RAPID trial was initially classified as a clinical trial of a medical device by the MHRA based on the inclusion of the BrighterSide smartphone app. Following removal of this intervention and on exit of the last participant allocated to BrighterSide in November 2023, the trial ceased to be a clinical trial of a medical device and under the regulation of the MHRA.

All participants already recruited to the BrighterSide arm were followed up to 6-month follow-up and completed involvement as per the study protocol.

Our trial included an internal pilot. Following review of the internal pilot recruitment data by the funder in August 2023, the monthly recruitment target was reduced from 50 to 35 participants per month effective from June 1, 2023.

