### Sample size

We will randomise a maximum of 1064 participants (approximately 335 Northeast London; 224 for Manchester, East London and Glasgow; and 111 for Oxford); a total study sample of 1118 participants including the 54 participants allocated to BrighterSide arm. We power for an expected difference in proportion of admission rates between arms of 7.5%, and an expected admission rate within 6 months in the TAU group of 15% (based on extensive audit data from our NHS Trusts). The design follows the methods outlined for MAMS designs with binary outcomes [29] calculated using nstagebin in Stata. It uses the same outcome at both stages and has a primary endpoint of 6 months after recruitment in each stage and the loss to follow-up rate is 5%. One-sided significance levels of 30% and 2.5% and powers of 92% and 90% are used in the 1st and 2nd stages respectively. The total sample size of 1064 represents the maximum possible sample size under the 2-stage MAMS trial design: the minimum sample size if both arms are dropped for futility at the interim analysis would be 684. The interim analysis will take place after 385 participants provide 6-month outcome data, which will occur in May 2024. The interim analysis may result in one or both interventions being removed from the trial at stage 1 (power = 92%, one-sided alpha = 0.3). The final analysis has 90% power and a one-sided alpha = 0.025. The overall family-wise error rate (FWER) is 0.0397. There is no need to account for multiple testing in a multi-arm trial with independent comparators [43]. We have allowed for a 5% missing data in the primary outcome (this is routinely available in electronic medical records, so we should have less than 5% attrition which are likely to be withdrawals).

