## Assignment of interventions: allocation

### Sequence generation

Randomisation (at the individual level) is independent and concealed using randomised-permuted blocks of random size administered by the King’s Clinical Trials Unit (KCTU; UK Clinical Research Collaboration registration 053) and which are not known to the study team. Randomisation is stratified by site. We use a 2:2:3 allocation in favour of TAU. In stage 2, we will keep the existing allocation or switch to 1:1 allocation if there is only one active intervention arm.

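### The intervention:TAU allocation ratio changes during the trial, but the stated models have no allocation-period term, so any drift in admission risk between periods would bias the comparison with TAU

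*Protocol article*

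**What the plan says.** All references are to the protocol article.

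- **Allocation so far.** Under Unplanned trial adaptations, the removal of BrighterSide brought this change: "Randomisation ratio changed from 1:1:1:2 favouring TAU to 2:2:3 favouring TAU". Each intervention against TAU therefore went from 1:2 to 2:3.
- **Allocation to come.** Under Sequence generation: "In stage 2, we will keep the existing allocation or switch to 1:1 allocation if there is only one active intervention arm".
- **Primary model.** Under Statistical methods for primary and secondary outcomes, for both stages: "we will use a generalised linear model that includes fixed effects for treatment, diagnosis and site using maximum likelihood estimation".
- **Secondary models.** The same section lists treatment, diagnosis, site, time and time-by-group effects, with a random participant effect. Time here is the 3- or 6-month visit, not the date of randomisation.
- **Other changes.** Unplanned trial adaptations opens with "Several important changes to the design occurred after the trial commenced". It then describes wider eligibility: crisis care within the previous 14 days, and PTSD or complex PTSD.

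The article mentions no period or stage covariate, no stratification of the analysis by period, and no combination of separate stage-wise estimates.

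**The concern.** Randomisation makes the arms comparable within a period of constant allocation. When periods with different ratios are pooled without a period term, TAU is over-represented early and the intervention late. If the underlying admission risk is stable, nothing follows. If it moves, part of the movement is read as a treatment effect.

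Stability cannot be taken for granted. Recruitment was to run from August 2022 to July 2025, eligibility was widened on the way, and the Background reports national compulsory admission rates rising year on year. Diagnosis and site adjustment removes drift that acts through case mix or site mix, such as part of the effect of adding PTSD. It does not remove a secular trend within site and diagnosis, or the effect of the 14-day rule.

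At stake are the primary effect estimate and its one-sided 2.5% test, mainly on the pre-planned path where one arm is dropped. The statement under Interim analyses that the p-value rule controls type I error whatever the true control event rate concerns the level of that rate. It does not cover a rate that moves between periods with different ratios.

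**Working it through.** **1. The plan's own figure.** Inputs from Sample size: 15% v 7.5%, one-sided alpha 0.025, power 90%, 5% loss, 2:2:3 allocation. With unpooled variance,

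TAU n = (1.960 + 1.282)² × [0.15×0.85 + (3/2)×0.075×0.925] / 0.075² = 432.6.

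The three-arm total is 432.6 × 7/3 = 1009.3, and 1009.3/0.95 = 1062, against the stated 1064. The design inputs are understood correctly.

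**2. Period sizes (intervention v TAU).** Realised counts by arm are not given, so they are taken from the ratios.

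- Period 1, at 1:1:1:2: the article's total is "not inclusive of the 54 participants randomised to BrighterSide at the time of dropping this arm". Those 54 imply 54 v 108, or 216 over PREVAIL, SAFETEL and TAU.
- Period 2, at 2:2:3: the article gives 684 as the minimum total if both arms stop at the interim. Taking this as the number randomised by that decision, 684 − 216 = 468, so 468×2/7 = 133.7 v 468×3/7 = 200.6.
- Stage 2, if one arm is dropped: 1064 − 684 = 380 at 1:1, so 190 v 190. The 380 is an assumption.
- Stage 2, if both continue: 380 at 2:2:3, so 108.6 v 162.9.

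**3. Shares of each arm by period.**

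- One arm dropped: retained arm (n = 378) 0.143 / 0.354 / 0.503; TAU (n = 499) 0.217 / 0.402 / 0.381.
- Both continue: intervention (n = 296) 0.182 / 0.451 / 0.367; TAU (n = 471) 0.229 / 0.425 / 0.346.

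**4. Formulas.** Assume no treatment effect and a common admission rate r_k in period k. Each arm's expected pooled rate is p = Σ share_k × r_k. Then

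- bias = p_TAU − p_int (positive favours the intervention);
- SE = √[p_int(1−p_int)/n_int + p_TAU(1−p_TAU)/n_TAU];
- one-sided alpha = P(Z > 1.96 − bias/SE).

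This is the unadjusted comparison on randomised numbers, ignoring the 5% loss and the interim look.

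**5. One case in full (20/15/10%, one arm dropped).**

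- p_int = 0.143×20 + 0.354×15 + 0.503×10 = 13.20%.
- p_TAU = 0.217×20 + 0.402×15 + 0.381×10 = 14.18%.
- Bias = 0.98 points, SE = 2.34 points, ratio 0.42.
- Alpha = P(Z > 1.54) = 0.062.

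**6. Range.** The rates are assumed; the three values apply to period 1, period 2 and stage 2.

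| Rates (%) | One dropped: bias, alpha | Both continue: bias, alpha |
|---|---|---|
| 16/15/14 | +0.20, 0.030 | +0.07, 0.027 |
| 18/15/12 | +0.59, 0.043 | +0.20, 0.030 |
| 20/15/10 | +0.98, 0.062 | +0.34, 0.034 |
| 14/15/16 | −0.20, 0.021 | −0.07, 0.023 |
| 12/15/18 | −0.59, 0.014 | −0.20, 0.021 |

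**7. Sensitivity to stage 2 size.** For a 5-point fall per period starting from 15%, the bias is 0.98 points with 380 in stage 2 and 0.95 points with 271. The assumed 380 is not critical.

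**8. Interim.** Of the first 385, 216 fall in period 1 and 169 in period 2. Period 1 then holds 53% of an intervention arm and 60% of TAU, so a 5-point shift gives 0.35 points of bias against an SE of 4.1 to 4.7 points.

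**9. With a period term.** Comparing within period and weighting by n_int×n_TAU/(n_int+n_TAU), the bias from a common shift is zero. Across the ten cases in step 6, the SE rises by at most about 0.02 points (for example 2.42 to 2.44 for 16/15/14% with one arm dropped).

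**The case against.** **The harm is conditional.** A reader might infer that the error rate is no longer 2.5%. The documents do not support that, because they give no drift in trial admission rates. The largest figure, 0.062, needs the rate to halve. The only evidence on direction, national admissions rising, points the other way, and there the test is conservative and the cost is some lost benefit. With both arms continuing, even a halving gives 0.34 points against a 7.5-point target. All of this stands, and it limits the severity.

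**The sample size after a drop is assumed.** The article calls 1064 the maximum and gives no total for the path with one arm dropped. This stands, but the result hardly depends on it (step 7).

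**A closed arm against later TAU.** A reader might also infer that the final model compares a dropped arm with TAU participants randomised after it closed. Under 20/15/10% that would shift the estimate by about 2.3 points (16.4% v 14.2%). The article does not say so: neither the statistical methods nor the interim section defines the control set for a dropped arm. The shift would also run against an arm already judged unpromising, so it would create no false positive. It is a rule to state, not an error found.

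**Eligibility and timing.** Part of the PTSD change is already handled by the diagnosis term, and neither eligibility change is dated, so their alignment with the ratio change is unknown. Both points stand.

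**The SAP may add the term.** It may, and a stated list of effects need not be exhaustive. But the article does not leave the covariates open. It names them for both stages and for the secondary outcomes, after the first ratio change was known and reported in the same paper.

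**Conclusion.** The point holds as a conditional one. The ratio has changed once and may change again, the stated covariates omit the period that governs it, and any shift in underlying risk not captured by diagnosis or site would bias the pooled comparison.

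For the drifts examined, the bias is 0.07 to 0.34 points in size if both arms continue. If one arm is dropped it is 0.2 to 1.0 points in favour of the retained arm when rates fall, and 0.2 to 0.6 points against it when they rise. One-sided alpha on that second path lies between about 0.014 and 0.062. These figures rest on assumed drifts, counts that follow the ratios, 684 randomised at the interim decision and 380 afterwards.

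This is a should-fix: modest in most scenarios, but it touches the confirmatory test on a planned branch and is almost free to remove.

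**What to change.** Add allocation period (randomised under 1:1:1:2, 2:2:3 or 1:1) as a fixed effect in the primary model at both stages and in all secondary models. Specify it before comparative results are seen. If a dropped arm is re-estimated at the final analysis, state that its comparator is restricted to TAU participants randomised while that arm was open.

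The cost is 1 to 2 degrees of freedom and a sentence or two in the SAP. No extra participants are needed, the only added variable is the allocation scheme in force at randomisation, and precision is essentially unchanged.

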Crisis teams are part of a UK strategy to provide community care to people with SMHPs who are experiencing a suicidal crisis with the aim of reducing PHAs [11]. However, more than half of the crisis team patients have an admission within a year of discharge from hospital [12]. People with an SMHP diagnosis, such as psychosis, bipolar and emotionally unstable personality disorder (EUPD), are the diagnostic groups most likely to have an admission following contact with a crisis team [13] and the majority of first admissions are due to suicidality [14]. Strategies to reduce PHAs include crisis planning, self/symptom management, relapse prevention and monitoring of suicidal risk [15]. Of these, interventions that focus on symptom management, relapse prevention and patient functioning can reduce the average number of readmissions [16]. However, the methodological limitations to existing studies, including risk of bias and inconsistent results, suggest that a high-quality trial of self-management strategies with admissions as the primary outcomes is required [16].

It is a deeply concerning fact that one in 100 deaths are by suicide and that over 700,000 people die per year because of suicide [17]. This has far-reaching emotional, social and economic impacts and it is crucial to have an evidence base for interventions that support people in a crisis to prevent suicide. Interventions that are designed to reduce suicidal ideation and behaviour may have also have an indirect effect on reducing admissions given the majority of first admissions occur in response to a suicidal crisis [14].

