### Outcomes

#### Primary outcome

The primary outcome is any admission to a psychiatric hospital admission over 6 months (treated as a dichotomous yes/no variable) which is obtained by screening the participants’ electronic patient records (EPR).

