#### Secondary outcomes

The secondary outcomes listed are collected by RAs at baseline, 3-month and 6-month assessment:Suicidal thoughts and behaviours are assessed using the Columbia-Suicide Severity Rating Scale (CSSRS), which is a valid and reliable interviewer rated measure [32, 33]. As the CSSRS is an interview-based measure with assessors rating participant responses for each CSSRS item, we require all assessors to undergo training in delivery of the interview and scoring is checked for reliability against a gold standard provided by an expert assessor ([name]). Training for the CSSRS is provided by an expert in the field of suicide intervention research ([name]) and all RAs are required to complete two CSSRS role plays with the trial management team to ensure proficiency of clinical skills (warmth, non-judgmental stance, active listening) and skill in asking the required questions as per the CSSRS interview schedule.Personal recovery using a service-user defined self-report measure of recovery, The Process of Recovery Questionnaire [34].Health status using the EQ-5D-5L self-report measure, which is a health status questionnaire shown to have acceptable validity in people with schizophrenia in European countries [35].The Recovering Quality of Life (ReQoL-10) self-report measure, which focuses on aspects of recovery and quality of life and was designed for use in a broad range of mental health conditions. It was collaboratively developed with service users and clinicians [36].Wider NHS and social care use will be assessed by the Economic Patient Questionnaire, which is conducted in an interview format and completed from the participants self-report regarding use of NHS and social care services. It also includes the Psychiatric Hospital Record, completed from the EPR [37].Anxiety will be measured using the GAD-7 a self-report measure [38].Depression will be measured using the PHQ-9 a self-report measure [39].Hope will be measured using the Adult HOPE Scale, which is an 8-item self-report questionnaire [40].Entrapment will be measured using the 4-item self-report Entrapment Scale Short-Form [41].Self-reported potential adverse effects of study participation measures on exit from the study at 6-month assessment [42].

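### Adding prior psychiatric admission, apparently available from the baseline Psychiatric Hospital Record, to the primary model would be a cheap, small gain in precision; the plan is valid without it

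*Protocol article*

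**What the plan says.** The protocol article (Statistical methods for primary and secondary outcomes) specifies, for the primary outcome at both stages, a generalised linear model, fitted by maximum likelihood, with "fixed effects for treatment, diagnosis and site". For each comparison with TAU, "we will report the difference in proportion of admissions as the estimate of treatment effect". The Interim analyses section uses the same model for the stage 1 futility decision at a one-sided p value of 0.3.

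The outcome is any psychiatric admission over 6 months, "treated as a dichotomous yes/no variable", obtained from electronic patient records.

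On baseline data, the Secondary outcomes section states that "The secondary outcomes listed are collected by RAs at baseline, 3-month and 6-month assessment". Of the Economic Patient Questionnaire it says: "It also includes the Psychiatric Hospital Record, completed from the EPR". Table 1 also marks the Psychiatric Hospital Record at enrolment, 3 months and 6 months.

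On design balance, the Sequence generation section says: "Randomisation is stratified by site". No other stratification factor is named.

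The Background and rationale section reports that "more than half of the crisis team patients have an admission within a year of discharge from hospital".

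**The concern.** A baseline measure of the same kind as the outcome is usually among the first covariates considered. Here that is recent psychiatric admission. A hospital record completed at enrolment most naturally describes earlier hospital use, because current inpatients are excluded. The model already adjusts for diagnosis, which is not a stratification factor, so adjustment for prognosis is accepted in principle; the closest counterpart of the outcome is nevertheless left out.

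Two things are at stake. The first is precision: a covariate that explains outcome variance narrows the interval around the risk difference at no cost in participants. The second is chance imbalance. Site stratification does not balance admission history, and at the interim the decision to keep or drop an arm rests on few events.

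**Working it through.** **Inputs from the protocol (Sample size; Sequence generation).** TAU rate 15%; target difference 7.5 points, so 7.5% on active treatment; allocation 2:2:3; one-sided alpha 0.025 with 90% power at the end and 0.30 with 92% power at the interim; 5% loss; maximum N 1064; interim N 385.

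**Inputs assumed.** Prevalence q of prior admission, 20% to 40%; odds ratio for the outcome, 2 to 4. The protocol gives neither.

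**Step 1. Reproduce the plan's sample size without the covariate.** With unpooled variance:

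n(TAU) = (1.960 + 1.282)² × [0.15×0.85 + 0.075×0.925/(2/3)] / 0.075² = 432.6

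Three arms: 432.6 × 7/3 = 1009.3. After 5% loss: 1009.3/0.95 = 1062, against 1064 stated.

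With 1064 × 0.95 = 1010.8 analysed (433.2 TAU, 288.8 per active arm), SE = √(0.1275/433.2 + 0.069375/288.8) = 0.0231. Then 0.075/0.0231 = 3.244, and power = Φ(3.244 − 1.960) = 90.0%. At the interim (165 TAU, 110 per active arm), SE = 0.0375 and power = Φ(2.002 − 0.524) = 93.0%, against 92% stated. The plan's figures stand and take no credit for adjustment.

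**Step 2. Upper figure for the gain.** Solve for the outcome risks without (p0) and with (p1) prior admission so that the overall TAU risk is 15%. Then R² = q(1−q)(p1−p0)²/0.1275, power = Φ(3.244/√(1−R²) − 1.960), and equivalent participants = 1064 × R².

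| q | OR | p0, p1 | R² | Final power | Equivalent N |
|---|---|---|---|---|---|
| 0.2 | 2 | 13.0%, 23.0% | 1.3% | 90.4% | 13 |
| 0.3 | 3 | 10.4%, 25.8% | 3.9% | 91.1% | 42 |
| 0.3 | 4 | 9.1%, 28.7% | 6.3% | 91.8% | 67 |
| 0.4 | 4 | 7.9%, 25.6% | 5.9% | 91.7% | 63 |

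This applies the TAU-arm R² to the whole comparison, so it is generous. The large-sample variance of the standardised risk difference, which uses the smaller gradient in the active arm as well, falls by 0.9% to 4.7% over the same grid. Final power is then 90.3% to 91.3%, worth 10 to 49 participants. Both sets are marginal figures, before allowing for what diagnosis and site already explain.

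**Step 3. Anchor on the background statement.** Half readmitted within a year, under a constant hazard (assumed), gives 1 − √0.5 = 29% at 6 months. With 15% overall and q from 0.1 to 0.4, the implied odds ratio is 2.7 to 7.2, variance falls by 1.4% to 7.6%, and final power is 90.4% to 92.1%. The order of magnitude is the same.

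**Step 4. Chance imbalance, at q = 0.3 and OR 3.** The SD of the difference in prevalence between arms is √[0.21 × (1/n1 + 1/n2)]. The gradient is 15.4 points in TAU and about 8.5 in the active arm, averaging about 12.

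- Final: SD 3.5 points. At the 95% limit, 6.8 points of imbalance shift the risk difference by about 0.8 points (SE 2.3).
- Interim: SD 5.6 points. At the 95% limit, 11.1 points shift it by about 1.3 points (SE 3.75), or 1.7 with the TAU gradient alone.

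The p = 0.3 boundary lies at 0.524 × 3.75 = 2.0 points. For an arm with the full 7.5-point effect, the chance of missing it is 7.0% on average. Given that adverse imbalance, it is 1 − Φ((7.5 − 1.3)/3.75 − 0.524) = 13%, or about 15% with the TAU gradient. Given the mirror-image favourable imbalance it is about 3%. These use the unreduced SE and are approximate.

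**Step 5. Room for another term at the interim.** Expected events are 165 × 0.15 + 2 × 110 × 0.075 = 24.75 + 16.5, about 41. With five sites and up to six listed diagnoses, the model already has up to 1 + 2 + 4 + 5 = 12 parameters.

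**The case against.** The strongest reply is that this is a preference about covariates. The model is pre-specified, contains the only stratification factor and adds diagnosis, which the background itself links to admission after crisis-team contact. No stated figure is wrong. That stands, and it is why the point is only a suggested improvement.

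Several stronger readings are tempting, and the protocol does not support them:

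- **That prior admission is an established strong predictor.** The background gives one readmission rate after discharge, with no comparison group. It suggests prediction but does not measure it.
- **That the baseline value is on file for everyone.** The record is scheduled at baseline, but its content, look-back and completeness are not described.
- **That the omission biases the result or leaves the trial underpowered.** Chance imbalance under randomisation is not bias. Its variation is already in the standard error, and type I error holds. Step 1 shows that the power holds too.

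The reply also notes that about 41 interim events against up to 12 parameters argue for caution before adding a term. That is a fair cost. A single binary term adds little to it, and a pre-specified fallback covers non-convergence.

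A detailed SAP is promised before the interim and may contain sensitivity analyses. The primary covariate set, however, is stated in the protocol and can be commented on as it stands.

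**Conclusion.** The point holds as a cheap improvement to a stated analysis choice, not as an error. Final power would rise from 90.0% to at most about 90.4% to 91.8%, with at most about 1% to 6% of outcome variance explained, and less after diagnosis and site. This rests on assumed prevalence of 20% to 40% and odds ratios of 2 to 4, and on the baseline record capturing earlier admissions.

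The more practical benefit is at the 385-participant futility look. There, an unlucky imbalance can shift the estimate by more than a point, against a boundary of about 2 points. Averaged over all possible imbalances, the interim gain is small. The stated sample size, power and type I error remain valid if nothing is changed.

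**What to change.** Before the interim analysis, pre-specify one binary baseline covariate: any psychiatric admission within the look-back that the baseline Psychiatric Hospital Record captures, with that look-back written down. Enter it as a fixed effect in the primary model at both stages, and report the risk difference as a standardised (marginal) estimate so that the effect measure does not change. Pre-specify a fallback for non-convergence, such as grouping sparse diagnosis categories.

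The cost is one line in the SAP and one more parameter. The record is already scheduled, so no new data collection should be needed provided it holds earlier admissions; confirm that and its completeness first. If the interim has already been run, keep the stated model as primary and add the covariate as a sensitivity analysis fixed before final unblinding.
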